### Measurements

Study visits and procedures per visit are summarized in *Figure*
*2*. A detailed overview of measurements is attached in *Table*
*1*.

**Figure 2 ehf215330-fig-0002:**
[figure not shown]
Study visits and procedures.

**Table 1 ehf215330-tbl-0001:** Study protocol

			V_1_	V_2_	V_3_	V_4_	V_5_	V_6_	V_7_	V_8_	V_x_
			Listing	Pre‐HT	Post‐HT	3M	6M	1Y	3Y	5Y	1/Y
General information	Inclusion/exclusion criteria		x								
	Informed consent form		x								
	Demographics		x								
	Medical history		x	x	x	x	x	x	x	x	x
	Medication		x	x	x	x	x	x	x	x	x
	KCCQ		x					x	x	x	
	Vital signs		x			x	x	x	x	x	
	ECG		x			x	x	x	x	x	
Cardiac metabolism	Diastolic and systolic LV—dysfunction	TTE	x					x	x	x	x
		RHC	x					x	x	x	
		MRI	x					x	x	x	x
		Hs troponin T	x			x	x	x	x	x	x
		Nt‐proBNP	x			x	x	x	x	x	x
	Macrovascular and microvascular complications of CAV	Angiography + IVUS/OCT	x					x	x	x	x
		FFR/CFR/MRR						x	x	x	
	Cardiac energy formation and consumption	CPX	x					x	x	x	
	Substrate metabolism and mitochondrial function	Respirometry						x	x	x	
	(Epi)genetics Transcriptomics	Leucocytes	x					x	x	x	
		Myocardium						x		x	
	Inflammation and allograft rejection	EMB						x	x	x	
		CRP	x		x			x	x	x	
Systemic metabolism	2‐h OGTT		x		x			x	x	x	
	Hyperglycaemia and T2D	Insulin	x		x			x	x	x	
		C‐peptide	x		x			x	x	x	
		FFA	x		x			x	x	x	
		FPG	x		x			x	x	x	
		RRPG	x		x			x	x	x	
		HbA1c	x		x			x	x	x	
		HOMA‐IR/beta	x		x			x	x	x	
		OGIS	x		x			x	x	x	
		PREDI‐M	x		x			x	x	x	
		T1D‐specific antibodies	x								
	Insulin resistance and metabolic syndrome	BMI	x		x			x	x	x	
		Waist–hip–ratio	x		x			x	x	x	
		Total Cholesterol	x		x			x	x	x	
		TG	x		x			x	x	x	
		HDL	x		x			x	x	x	
		LDL	x		x			x	x	x	
	AST/ALT		x		x			x	x	x	
	Liver function	GGT	x		x			x	x	x	
		AP	x		x			x	x	x	
		Bilirubin (direct/indirect)	x		x			x	x	x	
		INR	x		x			x	x	x	
		Antithrombin	x		x			x	x	x	
		Ammonia	x		x			x	x	x	
		Cholinesterase	x		x			x	x	x	
		Serum ferritin	x		x			x	x	x	
		Fib‐4 score	x		x			x	x	x	
	Kidney function	Urinalysis	x		x			x	x	x	
		eGFR	x		x			x	x	x	
		Albuminuria	x		x			x	x	x	
	Bone marrow	BM aspiration	x					x			
		Complete blood count	x		x			x	x	x	
	Intestine and microbiome	Faecal sample	x					x	x	x	

### Cardiac phenotyping

Left ventricular function will be measured by cMRI (3.0 T Ingenia Elition, PHILIPS Healthcare, Best, Netherlands), including measurements of volume, mass, function (systolic and diastolic), perfusion, and myocardial relaxometry. Feature Tracking analysis and 4D‐Flow measurements will be performed.^13^ Left‐ and right ventricular end‐diastolic and end‐systolic frames will be identified from short‐axis steady‐state free‐precession (SSFP) cine images with whole ventricle coverage from base to apex. LV mass, LV and right ventricular end‐diastolic and end‐systolic volumes, with the corresponding ejection fractions will be calculated using the Simpson disc summation method. Four‐, three‐, and two‐chamber cine views will be used to measure left and right atrial volume and function. Additionally, native relaxometric mapping of the myocardium (T1, T2, T2*), gadolinium contrast‐enhanced imaging (LGE), and post‐contrast relaxometric mapping (T1, extracellular volume) will be performed to assess myocardial inflammation, extracellular volume, and fibrosis. Dual‐sequence perfusion will be acquired following either vasodilator administration (regadenoson) or ergometer physical exercise. Myocardial perfusion images will be acquired at basal, mid‐ventricular, and apical levels in short‐axis slices, allowing automated pixel‐wise myocardial blood flow mapping and assessment of myocardial perfusion reserve for each of the 16 American Heart Association segments shown as a bull's‐eye plot. Quantitative perfusion will be performed as well. Certified CMR evaluation software will be used for all analyses (CVI42, Circle Cardiovascular Imaging Inc., Calgary, Alberta, Canada, or Sectra Workstation IDS7, Version 19.3.6.3510). For ^1^H MRS measurements, spectra will be acquired in the interventricular septum using a point‐resolved spectroscopy sequence (PRESS) with reduced spoiler areas and a spectral BW of 2000 Hz (1024 samples).^14^, ^15^ Metabolite cycling is implemented by adding the optimized Hwang pulse in front of the sequence.^16^ Spectra will be reconstructed in MATLAB using a customized reconstruction pipeline implemented in ReconFrame (GyroTools LLC, Zurich, Switzerland). Spectra will be fitted in AMARES to obtain CR/W and TG/W ratios.^17^, ^18^ If cMRI is not possible due to patient‐related factors, echocardiography will be applied. We have already tested comparability of different methods in the past.^19^

Coronary angiography together with intravascular imaging and intravascular physiology measurements will be conducted to diagnose CAV. Intracoronary imaging will be applied to identify intimal thickening of the coronary arteries.^20^ Optical coherence tomography (OCT) offers the highest imaging quality^21^ but requires contrast agent application and will thus be applied in patients with an estimated glomerular filtration rate (eGFR) > 30 mL/min using a Dragonfly™ OPTIS™ catheter (Abbott Laboratories, Illinois; USA). Patients with an eGFR <30 mL/min will be evaluated by intravascular ultrasound (IVUS) using an Eagle Eye Platinum catheter (Koninklijke Philips N.V., Amsterdam, The Netherlands). Diagnosis of coexisting or isolated microvascular disease will be achieved through intravascular physiologic assessment. Fractional flow reserve (FFR) analysis will be performed using a pressure‐sensitive guidewire. FFR is an index of the functional relevance of a coronary stenosis and is defined as the ratio of mean distal coronary pressure to mean aortic pressure at maximal hyperaemia. Following FFR, we will use a thermodilution‐based approach to determine coronary flow reserve (CFR), which is an index of coronary blood flow at rest and hyperaemic conditions and is considered a marker of microvascular disease.^22^ FFR and CFR measurements will be performed using a PressureWire™ X Guidewire (Abbott Laboratories, Illinois, USA). By dividing CFR by FFR while adjusting for aortic pressure, we will be able to calculate the microvascular resistance reserve (MRR), which is a recently developed tool for assessing the coronary vasodilatory capacity while correcting for both macrovascular coronary artery disease and vasodilator use.^23^

Allograft rejection will be evaluated by endomyocardial biopsy. Tissue specimens will be collected from the interventricular septum under standard fluoroscopic guidance for histochemical analysis at different time points post‐HTX. Endomyocardial tissue specimens will be analysed by cardiac transplant pathologists in accordance with the International Society for Heart and Lung Transplantation (ISHLT) criteria.^20^ Immunohistochemistry will be conducted to characterize inflammatory infiltrates, followed by quantitative digital image analysis. CD3+ lymphocytes will be identified using a CD3 antibody (Dako; dilution 1:25). Myocardial inflammation will be quantified by assessing CD11a+/lymphocyte function‐associated antigen (LFA)‐1+ lymphocytes/mm^2^, CD11b+/Mac‐1+ macrophages/mm^2^, CD45R0+ T memory cells (Dako, Glostrup, Denmark), and perforin+ cytotoxic cells/mm^2^. All antibodies will be procured from ImmunoTools (Friesoythe, Germany) and BD Biosciences (San Jose, California). An EnVision peroxidase‐conjugated anti‐mouse antibody (DakoCytomation) will serve as the secondary antibody, and immunohistochemical staining will be visualized using 3‐amino‐9‐ethylcarbazole (Merck, Darmstadt, Germany) as the chromogenic substrate. Slides will be counterstained with haematoxylin and mounted using Kaiser's gelatine R (Merck). Quantification of immunoreactivity will be performed through digital image analysis at 200× magnification, with results reported as the number of positive cells per square millimetre (mm^2^).

Furthermore, the Kansas City Cardiomyopathy Questionnaire (KCCQ) will be conducted to assess health status over time. KCCQ is a self‐administered, 23‐item instrument evaluating symptoms, physical function, social limitations, and quality of life, providing a comprehensive view of the patient's condition as described before.^24^ Participants will complete the questionnaire at multiple time points to track changes in their health status throughout the study. Cardiopulmonary exercise testing (CPET) will be employed to evaluate the cardiorespiratory function and exercise capacity of HTX patients. Participants will undergo a graded exercise test on a cycle ergometer with continuous measurement of respiratory parameters, including oxygen consumption (VO_2_), carbon dioxide production (VCO_2_), and ventilation (VE), utilizing a metabolic cart as described before using a Metalyzer® 3B CORTEX Biophysik GmbH (Leipzig, Germany).^25^ Additionally, myocardial mitochondrial metabolism will be assessed using high‐resolution respirometry (HRR) in permeabilized myocardial fibres as described previously.^26^, ^27^ In short, scar‐free myocardial tissue will be isolated, permeabilized with saponin, and prepared in a respiration medium. Single fibres will be weighed and placed in Oxygraph chambers for oxygen flux measurements at 37°C. Using predesigned protocols, various substrates and inhibitors, such as malate, octanoyl‐carnitine, ADP, glutamate, succinate, cytochrome C, oligomycin, FCCP, and antimycin A will be sequentially applied to assess different states of respiration, including coupled (P), uncoupled (E), and leak respiration (L).^28^

Total RNA from human heart biopsies will be isolated and used for library preparation following manufacturer protocols. HiFi/CCS sequencing will be performed using SMRTbell library preparation (PacBio) and analysed with SMRT Link v9.0. Long‐read sequencing will be conducted at the BMFZ, Heinrich Heine University Düsseldorf, using the Revio System. Short‐read RNA sequencing will use DNase‐digested RNA, quantified via Qubit and Fragment Analyser (Agilent). Libraries will be prepared using the VAHTS™ RNA‐Seq Kit for Illumina® and sequenced on HiSeq 3000/4000 (Illumina). Fastq files will be processed with bcl2fastq for trimming and demultiplexing. Long‐read data will construct a disease‐specific transcriptome, against which short‐read data will be mapped. Comparisons will be made to the GRCh38 reference transcriptome. Principal component analysis will assess mapping effects, incorporating clinical variables. Fastq analyses will be performed using CLC Genomics Workbench, with reads trimmed for quality and adapters.

Neoplasia will be screened as proposed by the ISHLT guidelines for post‐HTX care. Before HTX all patients undergo in‐depth screening for occult malignancies by whole‐body CT scans, screening for occult blood within the stool, and if indicated gastroscopy and coloscopy. Additionally, screening for dermal malignancies is performed by board‐certified dermatologists and urologists, and in female patients, gynaecological malignancies are excluded by urologists and gynaecologists. After HTX patients are at least annually screened for dermal malignancies by a dermatologist. Malignoma screening by urologists and gynaecologists is performed annually. Additionally, abdomen sonography and chest x‐ray are performed annually to screen for solid malignomas and lymph node enlargements. Gastroscopy and coloscopy are performed as indicated by detection of occult blood in stool or every 5 years after the age of 50.

Glucometabolic phenotyping will be conducted by measuring haemoglobin A_1c_ levels, fasting blood glucose, and 2‐h glucose above 200 mg/dL during an oral glucose tolerance test. Patients will be screened for diabetes‐associated antibodies to rule out type 1 diabetes (GAD65 [GAD] autoantibodies, IA‐2 [IA‐2] autoantibodies, zinc transporter 8 [ZnT8] autoantibodies, islet cell autoantibodies, insulin autoantibodies). In participants without insulin or sulfonylurea therapy with fasting blood glucose below 140 mg/dL, a 3‐h OGTT will be performed with blood sampling every 30 min after 75 g glucose ingestion. In addition, circulating insulin, c peptide, and free fatty acid levels will be measured in all patients. Insulin resistance will be assessed from the oral glucose insulin sensitivity index (3‐h OGIS) and the predicted M‐value (PREDIM).^32^ Additionally, insulin resistance will be estimated based on the homeostasis model assessment (HOMA‐2‐IR).^33^ In participants with confirmed diabetes mellitus, endotyping will be conducted in accordance with previous studies based on the clusters identified by Ahlqvist *et al*.^34^ and externally validated by other groups.^35^ Additionally muscle biopsies will be performed in selected cases to determine energy metabolism and inflammation within the skeleton muscle in diabetic and non‐diabetic transplant recipients.

Lipometabolic phenotyping will be conducted by time‐series measurement of circulating lipid levels (HDL, LDL, apolipoprotein B, triglycerides). In selected cases, MRI/MRS will be performed to analyse fat tissue distribution and detect ectopic fat deposits. Additionally, HDL function and quality will be determined via cholesterol efflux capacity assay (Abcam, USA). The influence of circulating lipids on the blood cells is also determined. The composition of the membrane of leucocytes and platelets, including the cholesterol content, is determined using liquid chromatography–tandem mass spectrometry (LC‐MS/MS) measurements. The resulting changes in membrane fluidity are analysed after incubation with fluorescent probes TMA‐DPH and DPH via measurement of anisotropy using a spectrophotometer (PerkinElmer, USA).

Additionally, leucocyte signatures will be determined. We will use flow cytometry for an initial assessment of leucocyte activation. Next, we will perform single‐cell sequencing to get deeper insights into leucocyte status over the time course. In addition, we will analyse epigenetic alterations in leucocytes. This will allow identification of certain leucocyte subsets which are associated with post‐HTX events like neoplasia and build the base for following mechanistic trials.

Platelet reactivity and thromboinflammation will be measured by different assays. First, circulating citrullinated histone H3 (H3cit)‐DNA complexes will be measured as previously described.^36^ This is a validated marker for circulating neutrophil extracellular trap (NET) formation. Second, we will investigate the interaction between platelets and leucocytes (especially neutrophils) via flow cytometry. Third, platelet reactivity in general will be analysed with flow chamber assays (BioFlux 200, I&L Biosystems GmbH, Germany), degranulation assays (Merck, Germany), and light transmission aggregometry (APACT 4004, LABiTec, Germany).

Medications, especially immunosuppressant agents, and their serum levels will be analysed during every visit (*Table* *1*). A standardized treatment protocol for immunosuppression post‐HTX minimizes the chance of bias by different immunosuppression regimes. Nevertheless, future multicenter sub‐studies may help to compare different immunosuppressant agents and their metabolic consequences. Dependency of glucometabolic and lipometabolic changes on medications will be analysed longitudinally.

### Sample size calculation

This study will prospectively include all new transplanted HTX recipients at our centre. We estimate 50 new transplantations per year. Additionally, we aim to recruit previously transplanted patients currently receiving follow‐up care at our centre. This cohort consists of 250 living HTX recipients. Based on an expected participation rate of 90%, we anticipate enrolling approximately 270 patients in the first year of the study. To address the initial hypothesis of the trial, metabolic deterioration post‐HTX is associated with impaired cardiac function and survival.

Based on previous studies, this sample size will yield a sufficient number of outcome events during the follow‐up of at least 100. Exact events rates based on glucometabolic disease are difficult to estimate from previous studies in this highly selected population, as neither glucometabolic disease nor respective outcomes have been as systematically or extensively screened for in previous trials. Thus, we estimate that, with a sample size of 400, at an alpha level of 0.05, assuming that 60% of patients develop glucometabolic disease after HTx and further assuming that the hazard for the primary outcome events is 35% higher (hazard ratio 1.35) in patients with glucometabolic disease, the estimated power for this study would be 0.8090 which is above the target of 0.8.

Beyond that, the trial is designed to allow further sub‐studies and even nested RCTs to address the aim of the study to achieve an in‐depth analyses of the interaction between metabolism, cardiac function, and inter‐organ communication and to reveal and test novel therapeutic regimens.

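### The stated power of 0.8090 matches a calculation with 400 events, one per patient, while the minimum of 100 events that the same section calls sufficient gives about 30% power at HR 1.35

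*Protocol article*

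**What the plan says.** Everything relevant is in the protocol article, Methods, Sample size calculation. The section first gives an event count: "this sample size will yield a sufficient number of outcome events during the follow‐up of at least 100". It then says that event rates by glucometabolic status are hard to estimate from earlier studies, and moves directly to power. The inputs are "with a sample size of 400, at an alpha level of 0.05, assuming that 60% of patients develop glucometabolic disease", and that "the hazard for the primary outcome events is 35% higher (hazard ratio 1.35) in patients with glucometabolic disease". The result is that "the estimated power for this study would be 0.8090 which is above the target of 0.8".

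The section names no formula and does not say whether alpha is one- or two-sided. The power statement includes no event probability, follow-up time or censoring. The minimum of 100 is the only event count in the article.

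**The concern.** In a time-to-event comparison, the information about a hazard ratio comes from the number of events. A sample size of 400 gives a power only after it has been converted into an expected number of events, and that step does not appear in the section. If the patient count was put in place of the event count, 0.8090 is the power of a study in which every patient has an event and nobody is censored.

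The event count that the section does give is far lower, and it is called sufficient. At stake is the only quantitative justification of the study size. It claims to clear the 0.8 target by less than one percentage point.

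**Working it through.** **Inputs**, all from the Sample size calculation section: N = 400; alpha = 0.05 (two-sided assumed, one-sided also tried); 60% exposed and 40% unexposed, so the ratio is k = 0.6/0.4 = 1.5 and the product of proportions is 0.6 × 0.4 = 0.24; HR = 1.35; stated power 0.8090; event floor 100. E is the number of events.

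**Formulas**

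- Freedman: power = Φ( √(E·k) · |1 − HR| / (1 + k·HR) − z ). Here |1 − HR| = 0.35 and 1 + k·HR = 1 + 1.5 × 1.35 = 3.025.
- Schoenfeld: power = Φ( √(E × 0.24) · ln HR − z ), with ln 1.35 = 0.3001.
- z = 1.960 two-sided, 1.645 one-sided.

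**Step 1: reproduce the stated figure.** Freedman, two-sided, E = 400: √600 × 0.35 / 3.025 = 2.834; 2.834 − 1.960 = 0.874; Φ = 0.8090. This agrees to four decimals. At E = 399 the result is 0.8080 and at E = 401 it is 0.8099, so within this formula the match singles out 400. Other choices at E = 400 do not match:

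| Variant at E = 400 | Power |
|---|---|
| Schoenfeld, two-sided, 60:40 | 0.8366 |
| Freedman, two-sided, 1:1 | 0.8458 |
| Freedman, two-sided, split reversed | 0.8527 |
| Freedman, one-sided, 60:40 | 0.8828 |
| Schoenfeld, one-sided, 60:40 | 0.9024 |

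**Step 2: power at the stated floor of 100 events.**

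- Freedman: √150 × 0.35 / 3.025 = 1.417; 1.417 − 1.960 = −0.543; Φ = 0.294.
- Schoenfeld: √24 × 0.3001 = 1.470; 1.470 − 1.960 = −0.490; Φ = 0.312.
- One-sided alpha 0.05: 0.410 and 0.431.

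**Step 3: power between the floor and full incidence** (two-sided, 60:40).

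| First events | Share of 400 | Freedman | Schoenfeld |
|---|---|---|---|
| 100 | 25% | 0.29 | 0.31 |
| 200 | 50% | 0.52 | 0.55 |
| 300 | 75% | 0.69 | 0.72 |
| 400 | 100% | 0.81 | 0.84 |

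**Step 4: events needed for 80% power.** With (1.960 + 0.842)² = 7.849:

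- Freedman: 7.849 × 3.025² / (1.5 × 0.35²) = 390.9, so 391 events (98% of 400).
- Schoenfeld: 7.849 / (0.24 × 0.3001²) = 363.1, so 364 events (91% of 400).
- One-sided alpha would still need about 287 (Schoenfeld) to 308 (Freedman).

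**Step 5: hazard ratio detectable with 80% power at 100 events.**

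- Schoenfeld: exp(2.802 / √24) = 1.77.
- Freedman: solving √150 · (HR − 1) / (1 + 1.5·HR) = 2.802 gives 1.87.

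**The case against.** Four points can be made for the article.

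*The count of 100 is a floor.* This stands. The article never says that 100 events are expected, so a reader who infers that the study has 30% power goes too far: 0.29 to 0.31 is the power at the stated minimum and not a forecast. For the same reason the two statements are not logically incompatible, since a minimum of 100 does not exclude 391. What fails is the claim that 100 would be sufficient for the effect assumed a few lines later.

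*The composite is very broad.* This also stands. Study endpoints counts any CAV above grade 0, any rejection above 0R or pAMR 0, infections needing professional care and raised liver enzymes, among others. Deterioration of glucose metabolism is itself a component. Read literally, the assumed 60% with glucometabolic disease would alone be 0.6 × 400 = 240 patients. A high event proportion is therefore plausible, but the article does not state one, and 240 events would still give only 0.59 to 0.62. Those events would also be the exposure itself, so they could not simply be counted as support for the comparison.

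*The formula is inferred.* This is correct, because none is named. Other routes reach 0.809: Schoenfeld with about 372 events two-sided or 294 one-sided, and Freedman one-sided with about 316. None of these counts appears in the article, whereas 400 does, and it matches to four decimals. That is strong evidence but not proof.

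*The two sentences may concern different things.* The event count follows a description of about 270 first-year patients and speaks of outcome events in general, while the power sentence refers to 400 patients and primary outcome events. Components can also recur in a patient, so 400 events need not mean one in each. The wording leaves both open. Neither reading changes the power at 100 events or provides the event proportion that 0.8090 needs.

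A reader might also infer that a null result would be misread as showing no association. Nothing in the article says how a null result would be interpreted, so that is not part of this point.

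**Conclusion.** The point holds in this form: the stated power is not supported by the section's own figures. The value 0.8090 corresponds to 400 events under a two-sided Freedman calculation, which indicates that patients were counted as events. At the minimum event count called sufficient, power for HR 1.35 is about 0.29 to 0.31. The 0.8 target is reached only with about 364 to 391 first events, that is, in 91% to 98% of patients.

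This rests on two-sided alpha 0.05, a 60:40 split, proportional hazards, and an analysis of first events. One-sided alpha raises power at the floor to no more than 0.43. True power may lie well above the floor value, because the composite may produce many more events, but the article gives no rate from which to judge by how much.

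**What to change.** Rewrite the power paragraph in terms of events:

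1. Replace 0.8090 with power by number of first events at HR 1.35: 0.29 to 0.31 at 100, 0.52 to 0.55 at 200, 0.69 to 0.72 at 300, and 0.80 at about 364 to 391. Name the formula and the sidedness of alpha.
2. State the proportion of patients assumed to have a first event over the planned follow-up, with its basis, and the power that this proportion gives.
3. Remove the statement that at least 100 events is sufficient for HR 1.35. If the floor stays in the text, say that the hazard ratio detectable with 80% power at that minimum is about 1.77 to 1.87.
4. If 0.8090 is kept, say that it assumes 400 events, meaning an event in every patient and no censoring.

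The cost is one reworded paragraph and a less favourable stated power. No extra patients are needed.
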